**Figure 3 fig3:**
[figure not shown]
Exercise units and durations of both intervention groups. This Figure shows the timetable of a week during the intervention. Sleep and activity questionnaires are filled out by both groups on a daily basis. In the experimental condition, participants will have aerobic exercise units 3-4 times per week, while participants in the control group do progressive muscle relaxation. During weekdays (Monday to Friday), participants in the experimental condition, will do Yoga and Juggling exercises, while participants in the control group listen to chapters of a scientific podcast on age-related topics.

To monitor adherence to the training plan, participants wear pulse watches (Garmin vivosmart 4) that they have to activate during the execution of their units. All recorded data are then synchronized with their individual study Garmin Connect account. This pseudonymized study account is created and set up by the study team and is connected to the mobile phone of the participant during the pre-assessment. Participants are informed and agree that all recorded activities can be read out by the study team. In case too many recordings missing, the study team contacts the respective participant to see if there are technical issues or other problems with the execution of the intervention.

After the intervention phase, the post-assessments take place. In general, the post-assessments comprise the same tests and measures as the pre-assessments, except for the omission of the ACE-III and the MWT-B.

After completion of the post-assessment, participants receive feedback about individual measures from the study. These include a summary of their results from the sports assessment, sleep and exercise data from the daily questionnaires, as well as feedback on whether the results of the cognitive screening test and the MRI were age-appropriate. All these information are sent to the participants in a PDF document via mail and are edited in graphs to be easily comprehensible. If gross pathologies are detected in the MRI or the score in the ACE-III falls below the cut-off of 87 points, participants are informed even before the end of the study.

### Data storage and management

All participant-related data are collected and assigned a pseudonymized study ID. It is not possible to draw any conclusion about the identity of the participant solely from the pseudonym. Only the principal investigator keeps a password-protected list in which pseudonyms are matched with participants’ real names and basic demographic information. This list is stored in the test center and will be saved for 10 years after the end of the study.

For all cognitive and psychological tests and questionnaires collected in the NPT lab of JUH in paper-and-pencil form or on the computer, only the study ID is used, and all data are instantly stored on the internal Hospital server and are password-protected.

MRI scans are done at the research MRI facility of JUH/Friedrich Schiller University. All data collected are stored on the clinical DICOM server and are only accessible with permissions.

Gut microbiome data are collected at participants’ homes. All tubes are labeled with the study ID of the respective participant. The samples are stored by the Integrated Biobank Jena (IBBJ) of the JUH in accordance with their rules of use and with the approval of the relevant ethics committee. Analysis of the stool samples will be done within the ITN SmartAge Consortium.^1^ For that purpose, all samples will be sent to Kiel University, Germany. The stool sample tubes will arrive in Kiel only labeled with participants’ study IDs.

During the eight-week intervention, participants wear pulse watches (Garmin vivosmart 4) and activate them during the execution of certain units. All recorded data are then synchronized with the Garmin Connect App, in which all participants are logged in with their respective study accounts. This account includes no personal data of the participants. When using the pulse watch for the walking units, participants can decide whether or not to use GPS while recording their activity. By analyzing activities for which GPS was used, it would be possible to draw conclusions about the area of residency of a participant. Therefore, all participants are informed beforehand and instructed on how to avoid GPS localization if desired.

### Data analysis plan

For the confirmatory analysis, we plan to test the primary outcome for group differences. To test the hypothesis that the specific intervention group has a higher impact on the primary outcome than the active control group, we will apply an ANCOVA within the framework of general linear models in which the group effect is tested on a two-sided level of significance of α = 0.05, with sex as the stratum and baseline VPS *C* as a covariate.

All statistical analyzes of the secondary outcomes will be carried out in an exploratory manner. All remaining cognitive measures will be analyzed in the same way as the primary outcome.

For the brain measures, we are going to investigate and compare the brain plasticity changes using structural MRI images. For this purpose, we will first implement a voxel based morphometry analysis to look for possible brain structural differences (total gray matter and white matter volume and region based). Then, after calculating the BrainAGE score using a machine learning framework and brain volumes, we will investigate any changes in individual BrainAGE score and brain plasticity induced by physical activity. We will furthermore investigate and compare potential changes in functional and structural brain connectivity within and across large scale brain networks. Functional connectivity will be analyzed by looking at changes in intrinsic resting state networks, and structural connectivity by analyzing changes in white matter fasciculi by using Diffusion Tensor Imaging (DTI).

The stool samples will be processed at Kiel University to perform 16S gene sequencing in order to assess the microbial composition of patients’ feces. Alpha and beta diversity analyzes, as well as constraint-based metabolic models of each sample’s microbial community, will be conducted. If any of the mentioned analyzes will show an association with the primary or a secondary outcome of this study, shotgun metagenomics, as well as metabolomics will be performed on a subset of the samples to increase the resolution of both bacterial composition and metabolic functional content. This will also allow validation of the modeling results and provide evidence for host or bacterial metabolites involved in the gut-brain metabolic cross-talk.

The exploration of the associations between cognitive, brain, and gut-microbiome data will be done using multiple linear regression analyzes. The cognitive measures of the post-assessment (primary outcome: VPS *C*) serve as dependent variables. The respective cognitive measures of the pre-assessment, sex, age, and IQ will be used as covariates. Changes in brain and gut-microbiome measures serve as independent predictors.

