Based on prior research, we expect that participants randomly assigned to the physical activity intervention group will show higher improvements in the cognitive outcome measures. We further hypothesize that these exercise-induced changes in cognition are associated with changes in brain structure and function, as well as alterations in the gut microbiome composition.

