### Outcome measures

Primarily, we aim at assessing the effect on cognitive functions measured by various standardized and non-standardized cognitive tests. As we are only including cognitively healthy participants, reaching a ceiling effect in some of the established clinical tests designed for measuring cognitive impairment in older individuals or patients with brain dysfunction might be a pitfall. Therefore, our primary outcome is visual processing speed (VPS) which is derived from an experimental psychophysical whole report task based on the theory of visual attention (TVA; Bundesen, 1990). By computational modeling, a person’s individual VPS, in numbers of objects processed per second, can be estimated. We will focus on VPS because it has been shown to decrease with age (McAvinue et al., 2012; Ruiz-Rizzo et al., 2019), it is especially affected in individuals at risk for dementia (Ruiz-Rizzo et al., 2017), and it has been shown to improve after an experimental intervention in healthy, older individuals (Penning et al., 2021). Regarding the procedure, firstly, we will test whether an eight-week physical fitness intervention increases VPS in healthy older adults, based on the results of a previous study by Penning et al. (2021).

Secondly, to explore the underlying mechanisms of the impact of physical activity on healthy cognitive aging we will test whether the changes in the cognitive outcome measures are related to changes in brain structure and function, and the gut microbiome composition.

The primary outcome of this study is the change from pre-to post-assessment of the visual processing speed *C* (in elements/s), derived from the whole report based on the TVA (Bundesen, 1990).

The secondary outcomes will be derived from five different data categories: Data obtained from cognitive tests, psychological questionnaires, Magnetic Resonance Brain imaging (MRI), gut microbiome samples, and physical fitness assessments. See Table 2 for detailed descriptions of outcome measures and scheduling of data collection.

**Table 2 tab2:** Outcome measures.

Variables	Instruments	Pre- and post-assessment
Primary Outcome: Visual processing speed *C*	Whole report task (TVA)	NPT session
Visual short-term memory capacity *K*	Whole report task (TVA)	NPT session
Visual threshold *t_0_*	Whole report task (TVA)	NPT session
Top-down control *α*	Partial report task (TVA)	NPT session
Cognitive speed	Trail-Making-Test Part A	NPT session

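### The regression linking cognitive change to brain and microbiome change omits randomized arm, so in a pooled model the association can be confounded by arm

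*Protocol article*

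**What the plan says.** The last paragraph of the Data analysis plan in the protocol article sets out the association model in three parts:

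- Outcome: "The cognitive measures of the post-assessment (primary outcome: VPS *C*) serve as dependent variables".
- Covariates: "The respective cognitive measures of the pre-assessment, sex, age, and IQ will be used as covariates".
- Predictors: "Changes in brain and gut-microbiome measures serve as independent predictors".

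Arm is neither a covariate nor a predictor, and no mediation model is described. The paragraph does not say whether the arms are pooled, and nothing restricts it to one arm.

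The same section does put arm into the primary model: "the group effect is tested on a two-sided level of significance of α = 0.05, with sex as the stratum". The remaining cognitive measures are to be analyzed in the same way. On status it says: "All statistical analyzes of the secondary outcomes will be carried out in an exploratory manner".

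The purpose of the association model is worded in two ways. The Introduction hypothesizes that "these exercise-induced changes in cognition are associated with changes in brain structure and function, as well as alterations in the gut microbiome composition". Outcome measures is looser: "we will test whether the changes in the cognitive outcome measures are related to changes in brain structure and function". That sentence nevertheless gives its purpose as exploring how physical activity acts on cognitive aging.

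**The concern.** This is not a detail left to a fuller plan. The article states the covariate set, and arm is missing from it.

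In a randomized trial, arm is the one variable expected to move both sides of this regression. Suppose training raises VPS C and, through an unrelated route, also shifts a microbiome or brain measure. In the pooled sample, people with a larger marker change then tend to have higher post-assessment C simply because more of them are in the exercise arm. Without arm in the model, the marker coefficient mixes this between-arm difference with the within-arm association. The problem arises when training succeeds on both fronts, which is what the investigators hope for.

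At stake is the reading of the mechanism question. A positive coefficient could mean that the marker relates to cognition, or only that training changed both. There may also be a practical consequence. The plan makes shotgun metagenomics and metabolomics on a subset of samples conditional on a microbiome analysis showing an association with an outcome. It does not say that this regression is the trigger, but it describes no other association model.

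**Working it through.** **Inputs from the protocol (Sample size).** Expected difference in C of 3 letters/s, SD 5, two-sided α = 0.05, 80% power, 45 per arm, raised to 50 per arm.

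**The plan's own figure.** A two-sample t-test with standardized effect 3/5 = 0.6 needs n = 44.59, rounded up to 45 per arm. Power is 0.804 at 45 and 0.844 at 50. The stated 45 is reproduced, and nothing below disputes it.

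**Assumptions not in the protocol.** The arm effect on the marker change, dM, is not given, so it is varied from 0 to 1.0 SD. The SD of 5 is taken as the residual SD of post-assessment C given baseline. One marker is tested at a time. Sex, age, IQ and baseline C are unrelated to arm and marker.

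**Size of the spurious slope.** Let dY = 0.6 be the arm effect on C in residual SDs, with 1:1 allocation (variance of the arm indicator 0.25) and no link between marker and C within arms. In the pooled sample:

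- cov(marker, C) = 0.25 × dM × dY
- var(marker) = 1 + 0.25 × dM²
- slope without arm = 0.25 × dM × dY / (1 + 0.25 × dM²)

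At dM = 0.5: 0.075 / 1.0625 = 0.071 SD, or 0.071 × 5 ≈ 0.35 letters/s per marker SD.
At dM = 1.0: 0.15 / 1.25 = 0.12 SD, or 0.12 × 5 = 0.60 letters/s per marker SD.
The true within-arm slope is zero in both cases.

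**Rejection rate.** The listed model was simulated with and without arm, 5,000 trials per setting, arm effect on C of 3, no within-arm link. The figures are the share of trials in which the marker coefficient has p < 0.05.

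| Marker shift (SD) | No arm, 45 per arm | No arm, 50 per arm | With arm, 45 per arm | With arm, 50 per arm |
|---|---|---|---|---|
| 0 | 4.9% | 5.3% | 4.9% | 4.9% |
| 0.2 | 5.9% | 5.6% | 4.7% | 4.7% |
| 0.3 | 6.7% | 7.7% | 4.6% | 5.4% |
| 0.5 | 9.7% | 10.7% | 4.8% | 4.6% |
| 0.8 | 16.9% | 17.7% | 5.3% | 5.3% |
| 1.0 | 22.6% | 23.8% | 4.7% | 5.2% |

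The simulation error near 5% is √(0.05 × 0.95 / 5000) ≈ 0.3 percentage points, so the result at 0.2 SD is barely above nominal. With 50 per arm, the mean simulated slope without arm was 0.37 letters/s at 0.5 SD and 0.60 at 1.0 SD, in line with the formula. With arm it was close to zero.

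**Cross-check at dM = 1.0, 50 per arm.** Residual variance without arm is 1 + 0.25 × 0.36 − 0.15²/1.25 = 1.072. With 94 residual degrees of freedom, SE ≈ √(1.072 / (94 × 1.25)) = 0.0955. The ratio is 0.12 / 0.0955 = 1.26, and Φ(1.26 − 1.96) ≈ 0.24, which agrees with 23.8%.

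**When there is no inflation.** With no arm effect on C, the rate without arm stays between 4.6% and 5.5% for every marker shift. With no arm effect on the marker, it is 4.9% and 5.3% (first row). The confounding needs both effects.

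**The case against.** The strongest reply is that the plan calls this work exploratory and that Outcome measures asks only whether the changes are related, which the listed model can address as a raw association. The confirmatory test includes arm and is not touched. The paragraph does not state that arms are pooled, and a regression within the exercise arm alone would not be confounded in this way. All of this stands and limits the weight of the point. It does not remove it: the Introduction aims the analysis at exercise-induced change, pooling is the likelier reading, and an exploratory label does not make a confounded coefficient easier to interpret.

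A reader might infer more than the documents support:

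- **That the model will report links that do not exist.** This is conditional on arm effects on both cognition and the same marker. Even at a 1.0 SD shift, roughly three quarters of trials would not falsely reject. The marker shifts are assumptions.
- **That exercise-induced change is never tested.** The group effect on VPS C is tested in the ANCOVA, the other cognitive measures are handled likewise, and the plan will examine BrainAGE and brain plasticity changes due to activity.
- **That an arm-by-change interaction is the missing test.** If training moves a marker and the marker moves cognition with the same slope in both arms, the interaction is zero although the mechanism is real. In a simulation of that case (45 per arm, 0.8 SD shift, common slope 0.5) the interaction rejected in 5.3% of trials. Equal slopes in the two arms do not count against the hypothesis.
- **That omitting the marker's baseline value biases the result through regression to the mean.** Noise in an unrelated marker's baseline does not by itself create a link with cognition: a check with the baseline omitted gave 5.2% rejection. Bias would need a further assumption that the protocol does not supply.

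**Conclusion.** The point holds in a limited form. The stated covariate set omits arm. In a pooled model, if training shifts both cognition and a marker, the marker coefficient is confounded by arm and does not isolate the hypothesized link. For a single marker with no within-arm link, the nominal 5% test rejects in about 6% to 24% of trials over assumed shifts of 0.2 to 1.0 SD, against about 5% with arm in the model.

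This rests on pooling, on the planned effect on C being real, and on marker shifts that the protocol does not give. For small shifts the inflation is negligible. It is a worthwhile improvement to the mechanism analysis, not a must-fix.

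**What to change.** Add randomized arm as a covariate to every association model in the last paragraph of the Data analysis plan, and state that both arms are pooled. Read the marker coefficient as the arm-adjusted association, and report it beside the estimated arm effect on that marker. The two together speak to the mechanism question; neither does so alone. The arm-adjusted coefficient remains an observational association within arms and should be described as such.

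An arm-by-change interaction or within-arm slopes may be reported to describe whether the association differs between arms, but not as the test of an exercise-induced association.

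The cost is a sentence of wording and one degree of freedom per model; arm is already recorded. Some precision is lost where arm and marker are correlated. For the same residual SD, the variance of the marker coefficient rises by the factor 1 + 0.25 × dM², which is 1.06 at a 0.5 SD shift and 1.25 at 1.0 SD, so the standard error rises by about 3% and 12%.

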### Methodological challenges

With the data collection starting in March 2022, COVID-19 regulations in Germany had to be taken into account. The future situation and development of the pandemic are not foreseeable. Therefore, data collection and the intervention had to be planned accordingly. Instead of in-person group sessions for the intervention units, we decided to lay this out as an online intervention. The participants can execute all of the units themselves without any contact with other participants. This way, changing contact regulations due to governmental decisions will not affect the feasibility of the intervention. All pre-and post-assessments could be conducted with respect to necessary COVID-19 hygiene measures. To minimize the risk of any participant being infected during these assessments, only participants vaccinated against COVID-19 are recruited.

Another potential risk factor arises with participants doing physical exercises without supervision. To decrease the chance of any cardiovascular incident, a physician checks every participant before starting the intervention. After that, participants are assessed concerning their physical fitness and individually instructed on how to conduct the intervention. In case of any problems during the exercises, the study team is always approachable and can provide individual advice based on communication with the Sports Medicine department.

## Ethics statement

This study was approved by the ethics committee of the Faculty of Medicine of Friedrich-Schiller University Jena. The studies involving humans were approved by ethics committee of the Faculty of Medicine of Friedrich-Schiller University Jena. The studies were conducted in accordance with the local legislation and institutional requirements. The participants provided their written informed consent to participate in this study.

